## Introduction

### Background and rationale {6a}

In 2050, one out of six persons (about 13.6 million people) in Germany will be 75 years or older [1]. With increasing age, the focus of medical care shifts to the maintenance of quality of life (QoL) and functional capacity, which enables older persons to care for themselves as long as possible. A threat to QoL and functional capacity of older individuals are cardiovascular diseases, such as coronary heart disease and degenerative diseases of the heart valves. These cardiovascular diseases will increase in prevalence and incidence as demographic changes occur [2]. Survival rates after cardiac procedures are increasing despite rising age and the associated increase in concomitant diseases. Essential for the high survival rate is the continuous advancement in cardiac medicine and the establishment of gentler interventional procedures [3]. Nevertheless, frail patients with reduced muscle mass, strength, and endurance have a threefold increased risk of postoperative morbidity and mortality [4, 5]. Older cardiac patients also have a significantly increased risk of suffering a cerebrovascular or cardiac event during or after surgery [6]. Especially in geriatric patients, decreased exercise capacity and loss of physical functioning before, during, and after hospitalization have a strong negative impact on QoL, self-determination and everyday resilience [7].

Cardiac interventions are often followed by a long period of convalescence. Postoperative/ postinterventional delirium occurs in 12 to 53% of patients and is associated with a poor long-term outcome in terms of nursing home admission, cognitive decline, reduced independence in daily life, and increased mortality risk [8]. In frail or delirious patients, mortality is up to 40% [9, 10]. It is clear, that older cardiac patients are in need of additional support in order to ensure that their QoL and functional capacity can be maintained—or even improved—after a cardiac procedure. One form of additional support for older patients is a preparatory program, so-called multimodal prehabilitation, which seeks to improve functional capacity, psychological and physical health prior to the cardiac procedure [11].

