### Sample size {14}

A total number of 422 patients is planned for this intervention trial. The number of cases was planned on a confirmatory basis in order to be able to answer the primary questions with a power of 80%. A total of 338 patients (169 per treatment group) is sufficient to show a clinically relevant difference of 0.045 points in EQ-5D-5L at t6 with 80% power at the generally accepted two-sided significance level of 5%. It is assumed that the common standard deviation of the EQ-5D-5L is 0.17 and that the observations on the covariates have an R-squared of 0.25. Since this is a longitudinal study, a dropout rate of up to 20% is assumed, so a total of 422 patients will be recruited. The case number calculation was performed in nQuery version 8. The definition of a clinically relevant difference of 0.045 was based on the publication of McClure et al. [62], who restricted a minimal clinically relevant difference to values between 0.037 and 0.069 [62]. Since the publication did not include results on the German population, a value was chosen that was approximately 10% lower than the average of the countries considered in the publication. The assumption of a standard deviation of 0.17 is based on observations by [63], who observed a standard deviation of 0.171 at baseline and a standard deviation of 0.170 at 12-month follow-up in a sample of 1927 diabetes-2 patients [63].

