## Data collection and management

### Plans for assessment and collection of outcomes {18a}

The various assessments to be applied in the different data collection dates are shown in Table 4 and in the translated approved study protocol [Additional file 1].

The medical history includes age, height, weight, hip to waist ratio, blood pressure, heart rate, cardiovascular risk factors, and other cardiac and non-cardiac conditions. Previous cardiac and vascular surgical procedures will be also documented. Sociodemographic data will be included in the database in the form of marital status and education level, among others. Routine laboratory chemistry data before and after the cardiac procedures will be incorporated into a standardized laboratory protocol. Furthermore, we will complete a cardiac surgery or cardiac intervention protocol detailing the cardiac procedure. The total length of inpatient stay, the length of stay in the intensive care unit, and the performance as well as duration of cardiac rehabilitation will be recorded. Likewise, before and after the cardiac procedure, the occurrence of dyspnea will be documented. Postoperative/postinterventional complications (e.g., hemorrhage, pleural effusions, pneumothorax, cardiac arrhythmias) as well as mortality after 30 days and 1-year are systematically recorded. In order not to overlook the occurrence of delirium, the patient record is reviewed. If there are signs of severe agitation or other delirious symptoms according to ICD-10, the patient is classified as delirious. All peri- and postoperative data will be collected from the hospital electronic database or routine clinical documentation.

General QoL will be assessed by EQ-5D-5L [24] and disease-specific QoL by HeartQol [30, 64].

Functional assessments include the SPPB [27, 65], 6-min walk test [37], and handgrip strength [35, 36]. Daily activity will be measured by Katz Index [25, 26].

Frailty will be identified with the CFS [48], the Mini Nutritional Assessment [39, 40], and in a subgroup analysis by Bioelectrical Impedance Analysis [38].

Cognitive function will be screened with MoCa [28, 29, 66], SMI [50], and IQCODE [46].

Psychosocial assessments include the HADS [31–33], Pittsburgh Sleep Quality Index [41–43], Maastricht Questionnaire [44, 45], SWE scale [51, 52], LOT-R [55], UCLA Loneliness Scale [56, 57], IPQ [58], and TEX-Q [59].

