## Statistical methods

### Statistical methods for primary and secondary outcomes {20a}

Details on statistical analysis are described in a statistical analysis plan (see Additional file 2). The primary endpoint EQ-5D-5L will be evaluated using a joint model for longitudinal data. Stratification factors of age, sex, participation in DMPs, and center will be included as covariates in the model. Time courses of EQ-5D-5L are presented longitudinally for each group, and survival rates are presented descriptively using Kaplan–Meier curves. Treatment effects are reported with 95% confidence intervals. The secondary endpoint HeartQoL is evaluated analogously to the primary endpoint. Secondary endpoints Katz Index, SPPB, MoCa, and HADS are evaluated using mixed linear models, with the factors time point, treatment, and the interaction, and the covariates age, sex, DMP participation, and center. Marginal means are calculated for inter- and intra-group comparisons, and treatment effects are reported with 95% confidence intervals. Likewise, for the analysis of the health economic outcomes, mean differences are calculated in mixed regression models. Because of the skewed distribution of the cost data, the non-parametric bootstrapping procedure, which is also used in the uncertainty analysis of the incremental cost-effectiveness ratio (ICER), is additionally used to calculate the standard errors of the regression parameters. For the analysis of cost-effectiveness, the net-benefit regression procedure is used. Details can be found in the Additional file 1 “Study Protocol”.

Statistical methods in the process evaluation:

For the process evaluation, exploratory sensitivity analyses will be performed to assess the impact of dose, reach, fidelity, and adaption on the intervention’s efficacy. For this purpose, interaction-terms between the treatment variables and these factors will be included in the mixed linear models described above. In addition to the intention-to-treat population, a population will be defined that started the intervention as intended and stays adherent during the follow-up period (starting and adhering estimand).

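### The covariate list leaves out baseline frailty, which the protocol itself treats as strongly prognostic and records at t1; the analysis stays valid but gives up a little precision

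*Protocol article*

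**What the plan says.** The section on statistical methods for primary and secondary outcomes {20a} fixes the covariates of the EQ-5D-5L joint model: "Stratification factors of age, sex, participation in DMPs, and center will be included as covariates in the model". HeartQoL is to be analysed in the same way. The mixed linear models for Katz Index, SPPB, MoCa and HADS carry the same four covariates. Survival is to be shown descriptively with Kaplan–Meier curves.

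Four other places bear on frailty:

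- Background and rationale {6a} says that "frail patients with reduced muscle mass, strength, and endurance have a threefold increased risk of postoperative morbidity and mortality".
- Plans for assessment {18a} names the instrument first among several: "Frailty will be identified with the CFS".
- Table 4 marks the CFS at t1, t2, t3 and t6. Sequence generation {16a} places randomisation after the baseline assessment.
- Sequence generation {16a} stratifies by centre, age (below 81 or not) and gender, and not by frailty.

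The article refers to a statistical analysis plan (Additional file 2) for details. That plan is not at hand. The covariate list itself is stated in the article.

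**The concern.** The plan gives a covariate place to participation in DMPs, a variable the article does not otherwise describe. It gives none to frailty, the prognostic factor for which the background quotes a size. Mortality, one of the two outcomes tied to that size, is co-primary. Neither the randomisation nor the model uses frailty, although a pre-allocation score will exist for the enrolled patients.

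A baseline variable that predicts the outcome, entered in a linear model, removes residual variance and narrows the interval for the treatment difference. It also adjusts for whatever imbalance in that variable happens to arise. If the arms turn out to differ in frailty, a prespecified adjustment is more credible than one chosen afterwards, particularly in a trial whose participants know their allocation. What is at stake is precision and credibility, not validity.

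**Working it through.** **Inputs from Sample size {14}.** Two-sided level 5%, power 80%, "a clinically relevant difference of 0.045 points in EQ-5D-5L at t6", "the common standard deviation of the EQ-5D-5L is 0.17", "the observations on the covariates have an R-squared of 0.25", 169 evaluable per arm (338), up to 20% dropout, 422 recruited.

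**Step 1: reproduce the plan.** Residual SD = 0.17 × √(1 − 0.25) = 0.1472. Standard error of the difference = 0.1472 × √(2/169) = 0.0160. Then 0.045/0.0160 = 2.81, and power = Φ(2.81 − 1.96) = 0.802. A noncentral t calculation gives 0.800 at 169 per arm. For dropout, 338/0.8 = 422.5 against the stated 422. The plan's figures stand without frailty in the model.

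**Step 2: add frailty.** The documents give no figure for the share of t6 EQ-5D-5L variance that CFS explains, so a range is assumed. With extra share e, the residual SD is 0.17 × √(0.75 − e), and the standard error shrinks by the factor √((0.75 − e)/0.75). Power is by the normal approximation.

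| Assumed extra share e | Reduction in SE | Power at 169 per arm | n per arm for 80% |
|---|---|---|---|
| 0 (as planned) | – | 0.802 | 169 |
| 0.01 | 0.7% | 0.808 | 166 |
| 0.02 | 1.3% | 0.813 | 164 |
| 0.05 | 3.4% | 0.829 | 157 |

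At e = 0.05 the 95% half-width goes from 1.96 × 0.0160 = 0.0314 to 0.0303. The saving of 12 per arm (169 − 157) equals 24 of 338 evaluable patients; at e = 0.01 it is 6 of 338.

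**Step 3: what chance imbalance does.** A one-standard-error imbalance in a covariate that explains 5% of total variance shifts the estimate by √0.05 × 0.17 × √(2/169) = 0.0041. As a share of sampling variance this is 0.05/0.75 = 6.7%, and it is already inside the standard error of 0.0160. A simulation of 20,000 trials per setting (40% frail assumed, no frailty adjustment) gave type I error of 0.048 with e = 0.05 and 0.050 with e = 0.10. The error rate is not inflated.

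**Step 4: mortality.** Assume 8% overall 12-month mortality, 20%, 30% or 40% frail, 211 per arm, and apply the threefold ratio in full.

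- The 95% chance difference in the frail share is 1.96 × √(2p(1 − p)/211) = 7.6, 8.7 and 9.3 percentage points.
- Non-frail risk is 0.08/(1 + 2p), so the frail/non-frail risk gap is 11.4, 10.0 and 8.9 points.
- The product is 0.87, 0.87 and 0.83 points of mortality difference.

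The standard error of that difference is √(2 × 0.08 × 0.92/211) = 2.6 points, with a half-width of about 5.2. Even an imbalance at the edge of the 95% range moves the estimate by about a third of one standard error, again already counted in the interval.

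**The case against.** The strongest reply is that nothing in the plan is broken. The model contains the factors actually used in the randomisation (centre, age, gender). Omitting a further prognostic variable under 1:1 randomisation leaves the test valid, and the planned power is reached. Table 4 holds other candidates (SPPB, 6-min walk, grip strength, MNA), so choosing the CFS is partly preference. Eligibility also narrows the frailty range: patients must be sufficiently independent, and Katz index 0 and NYHA IV are excluded. All of this stands, and it limits the point to an improvement. It does not show that adding the score does harm.

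Four stronger readings are tempting, and the documents support none of them:

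- **The primary comparison is biased, or imbalance goes uncorrected.** Steps 3 and 4 show that the variation is already within the interval.
- **The trial is underpowered without frailty.** It is not, on its own inputs. If the listed covariates explained less than 0.25, power at 169 per arm would be 0.78 at R-squared 0.20, 0.73 at 0.10 and 0.68 at 0. That questions the 0.25, not the omission of frailty.
- **The threefold figure measures the gain for quality of life.** It concerns postoperative morbidity and mortality in frail patients. It is neither an association with EQ-5D-5L nor a figure for the CFS.
- **Adjustment would sharpen the mortality result in the same way.** The article states only descriptive Kaplan–Meier curves. For a hazard ratio, adding a covariate changes the quantity estimated and need not narrow its interval.

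**Conclusion.** The point holds as a modest, low-cost improvement. The covariate list omits a prognostic baseline score that the trial already collects before allocation. The planned analysis remains unbiased, keeps its type I error, and has its stated 80% power.

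The likely gain for EQ-5D-5L is a standard error smaller by about 0.7% to 3.4% and power of about 81% to 83% instead of about 80%. This rests on two assumptions: that t1 CFS explains 1% to 5% of t6 variance, and that this comes on top of the planned 0.25. The article does not apportion the 0.25 among named covariates. If baseline EQ-5D-5L or other terms already carry part of the frailty information, the gain is smaller. No gain in precision is claimed for mortality.

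**What to change.** Prespecify the t1 CFS score, recorded before allocation, as an additional covariate:

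- in the joint models for EQ-5D-5L and HeartQoL, including any survival submodel;
- in the mixed models for Katz Index, SPPB, MoCa and HADS.

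State that the t2 score is never used for this purpose, because it is taken after the prehabilitation and may be affected by it. Make the change before unblinding, and give the same list in the protocol and the analysis plan. If frailty is left out on purpose, one sentence giving the reason would do.

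The cost is one line of text and one more parameter per model (with the score entered as linear), with no new data and no change to trial procedures. Any hazard ratio from a survival submodel would be conditional on frailty and should be reported as such.

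While that sentence is open, reconcile its wording with Sequence generation {16a}: it counts DMP participation among the stratification factors, but the randomisation is stratified only by centre, age and gender. That is a separate matter and does not depend on this point.

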### Trial design {8}

PRECOVERY is a confirmatory, randomized, controlled, two-arm parallel group, assessor-blinded multicenter intervention trial. If positive, we will confirm the efficacy of the multimodal prehabilitation intervention with regard to patients’ QoL, medical, cognitive, and psychosocial outcomes 12 months after an elective cardiac procedure. We will randomize 422 patients aged 75 years or older scheduled for an elective cardiac procedure to either (a) SMC (*n* = 211) or (b) a 2-week multimodal prehabilitation intervention (“Karl-Heinz”, *n* = 211) with an allocation ratio of 1:1 per hospital, patient’s age and gender with a follow-up period of 12 months. An additional component of the RCT is a detailed health economic analysis by the Department of Health Economics and Health Services Research, University Medical Center Hamburg-Eppendorf, Germany. Furthermore, an independent process evaluation in a mixed-methods design will be provided by the Department of General Practice of the University Medical Center Goettingen, Germany.

The primary aim is to demonstrate superiority of the intervention group compared to SMC group in terms of QoL and mortality 12 months after the cardiac procedure. The secondary aim is to show the superiority of the intervention group compared to the SMC group in terms of functional and cognitive capacity, heart-specific QoL, and activities of daily living after 12 months.

For the health economic analysis, we anticipate at least equivalence, a better non-inferiority in healthcare costs after 12 months in the intervention group compared to SMC group.

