## Assignment of interventions: allocation

### Sequence generation {16a}

After baseline assessment, randomization will be 1:1 stratified by study center, patient age (< 81 years vs. ≥ 81 years), and gender (block randomization with random block lengths). Randomization will be performed by unblinded study physicians at the recruiting centers. After randomization, the patient will be informed about the respective allocation. In case of allocation into the intervention group, the prehabilitation center will be contacted by the unblinded study physician. The individual outcome assessors at the recruiting centers remain blinded.

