### Methods in analysis to handle protocol non-adherence and any statistical methods to handle missing data {20c}

Participants will be considered adherent to the intervention if they complete the minimal requirements (see Table 3). For participants to be included, they must have baseline values and at least one follow-up value, then the missing data will be imputed using multiple imputation. Details on the type of multiple imputation will be added following a blinded data review.

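### The mixed model for Katz, SPPB, MoCA and HADS lists neither the baseline score nor a common baseline mean, so the 12-month comparison is less precise than the collected data allow

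*Protocol article*

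**What the plan says.** Statistical methods {20a} of the protocol article gives the four secondary scales "mixed linear models, with the factors time point, treatment, and the interaction, and the covariates age, sex, DMP participation, and center". It continues: "Marginal means are calculated for inter- and intra-group comparisons, and treatment effects are reported with 95% confidence intervals". It does not say whether t1 is an outcome visit in this model. It also does not say whether the treatment effect is the arm difference at t6 or the difference in change from t1. The section opens with a pointer: "Details on statistical analysis are described in a statistical analysis plan (see Additional file 2").

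The schedule (Table 4) has all four scales measured at t1 and again at t6. SPPB and MoCA are taken only at t1, t2 and t6. Sequence generation {16a} puts the baseline measurement before allocation: "After baseline assessment, randomization will be 1:1 stratified by study center". The informed-consent section labels the baseline assessment t0 rather than t1, but there too it precedes randomisation. To be analysed, patients need a baseline: "they must have baseline values and at least one follow-up value, then the missing data will be imputed using multiple imputation" (section {20c}).

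These endpoints carry the trial's secondary aim (Trial design {8}): "The secondary aim is to show the superiority of the intervention group compared to the SMC group in terms of functional and cognitive capacity".

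**The concern.** Baseline is measured before randomisation, so any arm difference at t1 is chance. An efficient analysis uses that knowledge: it either fixes the arms at one t1 mean or conditions on each patient's t1 score. The listed terms do neither.

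- **t1 is a level of the time factor.** This is the natural reading, because within-group comparisons are planned and without t1 SPPB and MoCA would have no within-group change from baseline. Treatment plus interaction then gives each arm its own t1 mean. With complete data and free arm means at every visit, the t6 marginal-mean difference is the plain t6 difference, adjusted only for age, sex, DMP participation and center.
- **t1 is not a level.** Baseline is then absent, since it is not in the covariate list either.
- **The reported effect is the difference in change from t1.** Baseline is used, but with a fixed coefficient of 1 instead of r, which over-corrects.

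On each reading, the confidence intervals for the secondary aim are wider than the data permit.

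**Working it through.** **Inputs.** The model terms come from {20a}, the visits from Table 4, and the timing of baseline from {16a}. Sample size {14} gives 169 evaluable per arm, 422 randomised (211 per arm) and dropout of up to 20%. The t1–t6 correlation r of the four scales is given nowhere; 0.4 to 0.7 is assumed here.

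**The plan's own figure.** The article states no precision or sample size for these four scales. The nearest figure is for EQ-5D-5L: a difference of 0.045, SD 0.17, covariate R-squared 0.25, two-sided 5% and 80% power.

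n per arm = 2 × (1.960 + 0.842)² × 0.17² × (1 − 0.25) / 0.045² = 168.03, so 169. This agrees with the article. The total also fits: 338 / 0.8 = 422.5, against 422 stated.

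Without the R-squared the same formula gives 225 per arm. The plan therefore counts on a 25% variance reduction from covariates for its primary endpoint. The article does not say which covariates supply it.

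**Variance of the arm contrast at t6**, complete data, equal SD at t1 and t6, in units of 2σ²/n:

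- t6 difference with free t1 means, or with t1 left out: 1
- difference in change from t1: 2(1 − r)
- baseline-adjusted, or common t1 mean: 1 − r²

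The saving against the t6 difference is r². The saving against the change contrast is 1 − (1 − r²)/[2(1 − r)] = (1 − r)/2.

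| r (assumed) | change contrast | adjusted | saving vs t6 difference | saving vs change | saving vs t6 difference, 20% missing at t6 |
|---|---|---|---|---|---|
| 0.4 | 1.20 | 0.84 | 16% | 30% | 13% |
| 0.5 | 1.00 | 0.75 | 25% | 25% | 21% |
| 0.6 | 0.80 | 0.64 | 36% | 20% | 32% |
| 0.7 | 0.60 | 0.51 | 49% | 15% | 44% |

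The complete-data interval for the t6 difference is wider than the adjusted one by 1/√(1 − r²) − 1, which is 9%, 15%, 25% and 40%.

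**Missing data.** The last column is a likelihood calculation with 211 per arm, of whom 42 lack t6, visits t1, t2 and t6, and one common correlation between visits. Example at r = 0.5: variance 0.01105 with free t1 means and 0.00868 with a common mean; 1 − 0.00868/0.01105 = 21%. Baseline now helps a little even with free means, because it informs the missing t6 values. Against the change contrast the saving under the same dropout is about 26%, 21%, 17% and 13%.

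**Simulation check.** 4000 simulated trials with 169 per arm gave a saving against the t6 difference of 16.5% at r = 0.4 and 47.5% at r = 0.7. The formula gives 16% and 49%.

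**Sensitivity to the listed covariates.** If age, sex, DMP participation and center already explained a shared 10% of the variance (an assumption), the remaining correlation would be (r − 0.1)/0.9, or 0.333 to 0.667. The saving would then be 11–44%.

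**The case against.** The best defence is that {20a} is one condensed sentence covering four endpoints, in an article that refers to an SAP and a full protocol not shown here. How baseline enters, the covariance structure and the exact contrast are usual SAP content, and this SAP may already deal with them. That would settle the matter if the article were silent. It is not: it names the factors and the covariates, and the endpoint's own baseline is not among them. An SAP that follows this text has the same weakness. One that departs from it leaves the two documents in disagreement.

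Several parts of the defence do stand:

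- Free t1 means are inferred from the listed terms, not stated.
- It would be too strong to say that baseline is never used. A change contrast uses it, and so does a likelihood analysis when t6 values are missing. The imputation planned in {20c} may also draw on baseline, but it does not adjust the t6 values that were observed.
- One correlation range is applied to four different instruments. Eligibility requires patients able to care for themselves, which may narrow the baseline spread of the Katz Index and put it at or below the low end of the range.

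A reader might also infer bias or a false-positive problem. The documents do not support that. The time-by-treatment model gives a valid randomised comparison; chance imbalance at t1 averages to zero over randomisation and is already reflected in the interval width. Nor can one infer that the secondary endpoints fall short of planned power, because the article sets no effect size or power target for them.

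**Conclusion.** The concern holds as a matter of precision on four secondary endpoints. On each reading of {20a}, the t6 comparison has larger variance than a baseline-adjusted or common-baseline analysis of the same data, for any r strictly between 0 and 1. The primary joint model is not part of this point.

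The size depends on the assumed r of 0.4–0.7. It is tempting to read 16–49% as this trial's loss, but the documents give no correlation for these scales, so it is an illustration. If the R-squared of 0.25 assumed for EQ-5D-5L came wholly from baseline and carried over to these scales, r would be 0.5 and the saving 25% with complete data, or about 21% with 20% missing at t6. Both conditions are assumptions.

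**What to change.** In Statistical methods {20a}, and in the SAP if it matches, replace the model for Katz, SPPB, MoCA and HADS by one of two forms:

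1. Keep t1 as a response with one mean common to both arms, and include treatment-by-time terms only for the post-randomisation visits. This form still yields the planned within-group comparisons from baseline.
2. Use only the post-randomisation visits as responses, and add the t1 score and its interaction with time as covariates.

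In both cases keep the listed covariates and name the t6 arm difference from that model as the reported effect. If the SAP already does this, bring the article's sentence into line with it.

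The cost is a short text change. All four scales are already collected at t1 and {20c} already requires baseline values, so no new data are needed. The first form has one parameter fewer than the free-mean model. There is no material downside.
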